### Study Setting

The trial will take place in selected Hillah city hospitals, which are local government organizations that have various pediatric and adult sections. In Iraq, there are 273 public hospitals spread all over the country [51]. Hillah city in Babylon province has 4 hospitals and 1 Babylon Oncology Center. The recruitment of participants will be conducted at the following 5 locations: Imam Sadiq Teaching Hospital (general hospital) with 492 beds, Babylon Maternity and Children Teaching Hospital (obstetric and pediatrics hospital) with 323 beds, Morgan Teaching Hospital (specialized center for tertiary health care), Al-Noor Hospital for Children (pediatrics hospital), and Babylon Oncology Center [52].

Participants will be recruited and stratified into the following groups: (1) critical care units (1 artificial kidney unit, 1 resuscitation emergency unit, 1 catheterization unit, 2 children’s emergency units, 1 emergency department, 1 maternity emergency unit, 1 morning resuscitation unit, 1 operation room, and 1 pediatric surgery unit); and (2) noncritical care units (1 blood disease unit, 1 chemo injection unit, 1 health insulation unit, 1 private suite, and 5 pediatric lobby units). Staff in the selected hospitals are not employed in 2 areas at the same time, and pediatric patients with several diagnostic classifications are managed and provided usual care. Recruitment for this study started in July 2020. There is a 2-year outline plan for the research, with likely changes along with primary analysis outcomes.

### Inclusion and Exclusion Criteria

The study will include nurses who (1) have been employed by Imam Sadiq Teaching Hospital, Babylon Maternity and Children Teaching Hospital, Al-Noor Hospital for Children, Morgan Teaching Hospital, and Babylon Oncology Center; (2) have completed their bachelor’s degree and have a master’s or doctorate degree in nursing sciences; (3) have been working for at least 3 months and are not expected to be moved to another internal unit during the research period (including morning and evening shifts); (4) provide nursing care for both male and female hospitalized patients aged ≤18 years; (5) use a computer (desktop or laptop) with access to the internet at home or work (phone line or internet access), or use a smartphone (Android 6.0+ or iOS 11.0+) with internet access (Wi-Fi or mobile data) to join the online training course; and (6) have a working email address or a working mobile number, and have access to a computer or smartphone with internet access to complete questionnaires in a web browser.

The study will exclude nurses who (1) are not interested; (2) are not employed for at least 3 months; (3) work in units other than the selected units; and (4) are enrolled in another experimental trial.

The evaluation of whether the exclusion criteria are met is performed by the investigator during the recruitment phase or according to the participant’s responses during the interview.

### Screening for Eligibility and Enrollment

The recruitment period is planned to start in July 2020. A total of 172 participants will be recruited in the RCT. Of these, 46.5% (n=80) will be recruited from Imam Sadiq Teaching Hospital, 26.2% (n=45) will be recruited from Babylon Maternity and Children Teaching Hospital, 7.6% (n=13) will be recruited from Morgan Teaching Hospital, 16.3% (n=28) will be recruited from Al-Noor Hospital for Children, and 3.5% (n=6) will be recruited from Babylon Oncology Center. Collaborations will be established with the selected hospitals to facilitate recruitment. The number of participants needed to ensure a sufficient recruitment rate has been determined (see the sample size section).

The recruitment process is outlined in Figure 1. The main investigator will submit the official approval form for conducting the research at the selected hospitals (Multimedia Appendix 1), and the approval form for the training course (Multimedia Appendix 2 and Multimedia Appendix 3), which will be hosted by the Continuing Nursing Education Unit (CNEU) at the Faculty of Nursing.

**Figure 1 figure1:**
[figure not shown]
Participant flow through the trial. CNEU: Continuing Nursing Education Unit; ELNEC: End-of-Life Nursing Education Consortium; PPC: pediatric palliative care; RCT: randomized controlled trial.

Eligible nurses will be invited to participate in the trial by the CNEU team in the selected settings. The unit will refer potentially eligible participants depending on a quick eligibility explanation that the main investigator submits to the unit. The documents are as follows:

Nomination form for the training course (Multimedia Appendix 4) for recruitment: Each participant will fill out this form, and the data will be used for contact with each participant. The data fields include name, email address, telephone number (Telegram, Viber, or WhatsApp service), current duty, type of practice unit inside the selected hospital, date, job description, academic qualification, a text box for random numbers in the upper left side of the form, and participant’s signature. The number of forms printed is according to the size of the estimated sample for the research (see the sample size section).Table of the estimated sample: This table presents the details of the estimated sample and the types of practice units inside the selected hospitals (Multimedia Appendix 5). Using this table, the person in charge of the CNEU in each selected hospital will select eligible participants.Informed consent form (Multimedia Appendix 6)

Referral to the trial will take place after the CNEU in each selected hospital has selected participants according to the table of estimated sample size that will be provided to the CNEU and the current practice unit (usual procedure). Participants will be recruited through the unit team in the selected hospitals. Participants are provided with an invitation letter that includes written information about the project and numbered, opaque, sealed, and stapled envelopes that contain the nomination form for the training course. The written information provides 2 ways to contact the researcher, if the participant is interested in the project: (1) by email and (2) by telephone (call or instant message by Telegram, Viber, or WhatsApp message). The nomination forms for the training course filled out by candidates are placed in large (A4) sealed envelopes and sent to the CNEU at the Faculty of Nursing that will host the web-based training course.

The start of the study will involve preparation of formal and essential approvals through the academic professor (HJ) responsible for the CNEU at the Faculty of Nursing and coordination with the Babylon Health Department, to obtain official agreements for sample collection according to the study criteria. The candidate envelopes will be opened and the candidates will be entered in an Excel spreadsheet. The information entered in each form will be added in sequence, and the Excel spreadsheet will be backed up, printed, and kept in a safe and secure location. A copy of the spreadsheet will be sent via email to the main investigator to contact the participants via their provided email addresses or phone numbers (Telegram, Viber, or WhatsApp). The enrollment process is outlined in Figure 1. If candidates are eligible and willing to participate, the informed consent form will be signed and the main investigator will contact each participant and send a link to the web-based baseline questionnaire via email or social communication apps (Telegram, Viber, or WhatsApp). Then, randomization will be performed via a web-based randomization system (see the randomization section).

Participants can return the signed informed consent form in a prestamped envelope provided by the unit or can take a picture of the signed consent form and send it via a text message to the main investigator. Subsequently, the main investigator will contact the participants, inform them about the results of the random distribution, and provide instructions according to the group that was randomly chosen (control or intervention group). All instructions will be completed on the phone or via text message, and participants will receive a link to a website from the main investigator (Multimedia Appendix 7), which provides all instructions and details of participation in the training course (also presented in Arabic).

In the CNEU, randomization will be performed. If randomized to the ELNEC-PPC web-based training course in addition to usual care (intervention group), participants will be sent a link to the website that has all instructions for enrolling and registering in the training course and assistance on how to maintain access via instant messaging or email. Moreover, participants will be given information about their follow-up assessments and how to contact the main investigator if needed. If a participant declines to participate, the main investigator will ensure that the information from the baseline questionnaire is deleted. If randomized to usual care, participants will be instructed on the principles of usual care and will be given the same information as provided to the intervention group about their follow-up assessments and how to contact the main investigator if needed. The flow of participants through the trial is described in Figure 1.

### Randomization

Participants will be randomized to either (1) ELNEC-PPC web-based training as well as usual care or (2) only usual care. The randomization involves block randomization plus permuted blocks of random size known to the researcher and stratified by the type of unit (ie, critical care unit and noncritical care unit). The allocation ratio between the intervention and control groups is 1:1. Randomization will be performed using the Sealed Envelope website [53].

Randomization involves generating random numbers using a computer. The numbers are distributed and written on the nomination forms for the training course in the text boxes on the top of the forms. According to the sample size, the first random number represents the intervention group and will be written on the form with the code “T,” and the random number for the control group will be written with the code “C.” The forms are placed in sealed envelopes, and these are mixed and placed in a large sealed envelope (A3) (Multimedia Appendix 8). These steps represent the randomization process performed by a nurse. A video is made of the process of preparing the sealed envelopes, with the participant details visible. A second researcher will later view the video to ensure the accuracy of the process. Corresponding envelopes will be opened only by the participants who select them, and they will be allocated accordingly. The enrolled participants will complete all baseline assessments.

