### Blinding

This is a single-blinded study, and the participants are not blinded to group allocation. Examination and interpretation of the study results will be achieved by investigators blinded to group allocation. Once the study is completed, a copy of the data will be extracted in a pseudonymized form for statistical analyses. The information concerning the group allocation will be added to the data set with the intervention and control groups categorized as T and C, respectively. This work is done under a camera for documentation later (by supervisors), and the complete data entry is performed with blinding of the main researchers. The randomization key (ie, document with group details) will be kept with supervisors. They will provide the randomization key to the researchers once blinded interpretation of the results is finalized.

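### The Randomization section says the researcher knows the random block sizes, which weakens allocation concealment in an open trial; how much becomes predictable depends on sizes and a mechanism that the protocol does not settle

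*Protocol article*

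**What the plan says.** The Randomization section specifies "permuted blocks of random size known to the researcher and stratified by the type of unit", with two unit-type strata and 1:1 allocation on the Sealed Envelope website. It states no block sizes. It also does not say whether the researcher knows the size of each successive block or only the set of possible sizes.

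Other sections bear on who could use that knowledge:

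- **Screening for Eligibility and Enrollment.** The main investigator receives the candidate spreadsheet and sends the baseline questionnaire link, after which a web-based system randomizes. Then "the main investigator will contact the participants, inform them about the results of the random distribution". The nomination form records the practice unit, so the stratum is visible. The education unit in each hospital makes the first selection of candidates.
- **Inclusion and Exclusion Criteria.** "The evaluation of whether the exclusion criteria are met is performed by the investigator during the recruitment phase". Lack of interest is one of the exclusion criteria.
- **Blinding.** Participants know their arm. "The randomization key (ie, document with group details) will be kept with supervisors", and the blinding of researchers concerns data entry and the examination and interpretation of results.

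The Randomization section also describes a second procedure. Forms coded T or C go into sealed envelopes, the envelopes are mixed, and participants pick and open them.

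**The concern.** Block size is varied at random so that a person who sees past assignments cannot tell where a block ends. Here the protocol says outright that the researcher has the sizes; this is not a detail left to a fuller document. The main investigator learns every past assignment by announcing it and can see each nurse's stratum. If that person also has the sizes, the last assignments in a block can be worked out before the next nurse is allocated.

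Someone who knows the next arm can hurry, delay or discourage a particular nurse. That is selection bias, and randomization no longer protects against it. The primary outcome rests partly on a questionnaire that nurses complete about their own practice, so a difference in motivation between arms at entry could pass into the result. Keeping the key with supervisors does not prevent this, because the prediction needs only the past assignments and the block sizes.

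**Working it through.** The protocol gives no figure for predictability, so there is none to reproduce. The check asks what share of assignments is certain in advance under each reading.

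**Inputs**

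- Ratio: "The allocation ratio between the intervention and control groups is 1:1" (Randomization).
- Strata: two, "stratified by the type of unit (ie, critical care unit and noncritical care unit" (Randomization).
- Total: "A total of 172 participants will be recruited in the RCT" (Screening for Eligibility and Enrollment).
- Block sizes: not stated ("The randomization involves block randomization plus permuted blocks of random size"). Assumed range 2 to 10, with 4 and 6 as the central case.
- Stratum size: assumed 86 each, used in steps 3 and 5.

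**Step 1. Size of each block known, all blocks equal.** Take a block of 2k with k nurses per arm. An assignment is certain when all k places of the other arm have already been used. Among that assignment and those k places, it comes last with probability 1/(k+1). So the certain share is 1/(k+1).

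| Block size | k | Certain share | Of 172 |
|---|---|---|---|
| 2 | 1 | 1/2 = 50.0% | 86 |
| 4 | 2 | 1/3 = 33.3% | 57 |
| 6 | 3 | 1/4 = 25.0% | 43 |
| 8 | 4 | 1/5 = 20.0% | 34 |
| 10 | 5 | 1/6 = 16.7% | 29 |

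**Step 2. Mixed sizes, order known.** With sizes equally likely, the share is the sum of 2k/(k+1) divided by the sum of 2k.

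- {4,6}: (1.333 + 1.5)/10 = 28.3%
- {2,4,6}: (1 + 1.333 + 1.5)/12 = 31.9%
- {4,6,8}: (1.333 + 1.5 + 1.6)/18 = 24.6%
- {4,8}: (1.333 + 1.6)/12 = 24.4%
- {2,4}: (1 + 1.333)/6 = 38.9%

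**Step 3. Only the set of sizes known.** In 800 simulated lists of 86 per set, every block position consistent with the past assignments was tracked. An assignment counted as certain when all of those positions agreed.

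| Set | Certain share | Of 172 |
|---|---|---|
| {4,6,8} | 2.4% | 4 |
| {2,4,6} | 4.1% | 7 |
| {4,6} | 5.4% | 9 |
| {4,8} | 7.3% | 13 |
| {2,4} | 11.0% | 19 |

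**Step 4. Best guess rather than certainty.** Completed blocks are balanced, so the running imbalance in a stratum equals the imbalance within the current block. The best guess is always the arm that is behind, and it needs no knowledge of sizes. For a block of 2k its accuracy is [k + (4^k/C(2k,k) − 1)/2]/(2k).

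- Size 4: [2 + (16/6 − 1)/2]/4 = 70.8%
- Size 6: [3 + (64/20 − 1)/2]/6 = 68.3%

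The simulations of mixed sets in step 3 gave 68% to 72%. Knowing the sizes therefore adds certainty, not average accuracy.

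**Step 5. Mixed envelopes.** If the envelopes in a stratum of 43 + 43 are truly mixed, the certain share is 1/44 = 2.3%. That is 2 × 43/44 = 1.95 assignments per stratum, about 4 of 172.

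**The case against.** The strongest reply is that the envelope procedure is the one described in most detail. Mixing would destroy block order, so knowing the sizes would reveal almost nothing. This stands as far as it goes. But the enrollment text says allocation is by a web-based system and the Randomization section names the website, so the protocol describes two mechanisms that do not fit together. The envelope text does not make the statement about block sizes sound.

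A reader might infer that one person screens, contacts and informs every nurse. The documents support the contact and the informing. On screening, the hospital education unit selects candidates first and the exclusion check is given only to an unspecified investigator. The researcher who knows the sizes is likewise not named as the main investigator. Hospital quotas are fixed and candidates are listed before the investigator contacts them, which narrows the room to steer without removing it.

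A reader might also infer that withholding the order of the sizes brings certain predictions to 1% or less. That follows only if certainty is counted solely where the imbalance reaches half the largest block. The assignment history reveals more, as step 3 shows.

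Finally, the wording may be a slip for the opposite meaning. The article's English is uneven in places, and the design is called investigator-blinded. If so, the text still states the wrong thing and needs the same correction.

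**Conclusion.** The point holds in conditional form. A stated rule lets a researcher know the block sizes in an open trial whose main investigator sees past assignments and speaks to nurses before allocation. That defeats the purpose of random sizes and weakens concealment.

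The size rests on three assumptions: what exactly is known, how large the blocks are, and whether nurses are allocated one at a time from the web list.

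- **Each block's size known:** 25% to 33% certain for sizes 6 and 4; 17% to 50% across sizes 10 down to 2.
- **Only the set known:** about 2% to 5% for {4,6,8}, {2,4,6} and {4,6}; up to about 11% for {2,4}.
- **Mixed envelopes:** about 2%.

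A reader might take a quarter to a third as a property of this trial. The documents do not support that, because they give neither the sizes nor the order known. Nor do they show that anyone used such knowledge. This is a weakness that should be corrected, not evidence that the result is biased.

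**What to change.** 1. In Randomization, replace the words that give the researcher knowledge of the sizes. State that the block sizes and the list are set up by the supervisors who already hold the key under Blinding, and are withheld from anyone who recruits, contacts or informs nurses until the last nurse is allocated.
2. Reconcile Randomization with Screening for Eligibility and Enrollment so that one concealed mechanism is described, either the web system or the envelopes. Release each assignment singly, after consent and the baseline NoMAD are recorded.
3. If allocation is complete, changing the wording cannot restore concealment. The article says that recruitment opened in July 2020 and the last training was in August 2020, so this is likely. In that case, report which mechanism was used, who knew the block sizes, and whether they knew each size or only the set.

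The cost is a few sentences and, if allocation is still open, a change in who sets up the web list. No extra participants are needed. The change removes most certain predictions under the web list. It does not remove the advantage of guessing the arm that is behind (step 4), which comes from seeing past assignments.

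### The protocol describes two incompatible allocation procedures, and the envelope procedure neither keeps the permuted blocks nor secures concealment

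*Protocol article*

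**What the plan says.** The protocol article covers allocation in two adjoining Methods sections.

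**Screening for Eligibility and Enrollment.** With the invitation letter, nurses receive "numbered, opaque, sealed, and stapled envelopes that contain the nomination form for the training course". The form has a box for a random number. The nurse completes and signs it, and it goes back to the education unit (CNEU) at the Faculty of Nursing. There the envelopes are opened, and the details are entered in a spreadsheet that is emailed to the main investigator. Consent and the baseline link are described next, and after them: "Then, randomization will be performed via a web-based randomization system", with a pointer to the randomization section. A later paragraph places randomization in the CNEU.

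**Randomization.** The method is block randomization with "permuted blocks of random size known to the researcher and stratified by the type of unit", and "The allocation ratio between the intervention and control groups is 1:1". The Sealed Envelope website is named. The text then turns to paper: "The numbers are distributed and written on the nomination forms for the training course in the text boxes on the top of the forms", together with the code T or C. "The forms are placed in sealed envelopes, and these are mixed and placed in a large sealed envelope (A3"). Finally, "Corresponding envelopes will be opened only by the participants who select them, and they will be allocated accordingly". The sentence on baseline assessments comes last.

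**Statistical Analysis.** The model for the NoMAD score treats differences between the arms at baseline as coincidental.

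**The concern.** The two sections cannot both describe what is done. In one, a web system assigns the arm after consent and the baseline link. In the other, the arm is whatever code lies in the envelope that the nurse picks. The cross-reference from the first to the second does not help, because the section it points to describes the envelopes.

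Two things are at stake. First, the envelope procedure may not deliver the stratified permuted blocks that the protocol claims. Second, the arm code is on a document that nurses and staff handle during recruitment. If the arm can be known before a nurse is committed to the trial or has answered the baseline questionnaire, enrolment and self-reported baseline NoMAD could depend on it. Treating baseline differences as coincidental would then no longer be justified, and no later analysis can fully repair that.

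**Working it through.** **1. The two accounts side by side**

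| Feature | Screening for Eligibility and Enrollment | Randomization |
|---|---|---|
| Mechanism | Web-based system | List from a website, then coded forms in mixed envelopes |
| Who determines the arm | The system | The nurse, by selecting an envelope |
| Position relative to baseline | After the baseline link is sent | Not stated; baseline is mentioned last |
| Nomination form | Sent with the invitation, filled out, returned, opened by staff | Carries the number and the T/C code |

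The mildest reconciliation is that the website produces the list and a nurse copies it onto forms. The envelopes are then mixed and selected, so the arm still does not come from the listed order.

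**2. Block order**

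A permuted-block list balances the arms only if assignments are used in sequence within each stratum. Mixing removes the sequence, and selection by the nurse does so again. The envelopes are called numbered, but no rule for opening them in number order is given. The blocks are lost whether or not the strata are kept apart.

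**3. Stratification, if there is one pool**

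Inputs from the Sample Size section: 86 per arm, so N = 172 envelopes with K = 86 coded T. The hospital quotas agree: 80 + 45 + 13 + 28 + 6 = 172. The stratum size m is not shown, so it is assumed. The plan gives no imbalance figure to reproduce.

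If m nurses of one stratum draw from the single pool, the number T is hypergeometric:

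Var(T) = m × (K/N) × (1 − K/N) × (N − m)/(N − 1), and SD(T − C) = 2 × SD(T).

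For m = 86: Var(T) = 86 × 0.5 × 0.5 × 86/171 = 10.81, SD(T) = 3.29, SD(T − C) = 6.58.

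| Stratum size (assumed) | SD of T − C | P(difference above 4) | P(difference of 10 or more) |
|---|---|---|---|
| 40 | 5.6 | 37% | 10% |
| 60 | 6.3 | 42% | 15% |
| 86 | 6.6 | 45% | 17% |

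For comparison, with blocks of 2, 4 and 6 (assumed) used in order, the difference never exceeded 2 in 20,000 simulations at each of these stratum sizes.

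If the strata were mixed separately, with equal numbers of T and C, and every envelope was used, each stratum would end balanced. The blocks would still be lost.

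**4. Concealment**

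There are two plausible readings of when the code is written.

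- *Before the form goes out.* The nurse has the code at nomination. Staff who open the returned envelopes, and possibly the main investigator through the spreadsheet, can have it before consent and baseline are described.
- *After the form comes back.* The code is written on the form of an identified nurse. Whoever writes it can link arm to person, and the preparation is filmed with participant details in view.

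Neither reading secures concealment.

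**The case against.** The strongest reply is that the documents show a contradiction to be reconciled and do not show that allocation is exposed early. Much of this stands.

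- *A reader might infer that nurses receive the form with T or C already on it.* No sentence says so. Randomization in the CNEU, and participant details visible during envelope preparation, allow coding after the form is returned.
- *A reader might infer that baseline is completed after allocation.* That rests only on sentence order in the Randomization section. The other section puts the baseline link first. It also provides for deleting baseline answers when a participant declines, which suggests that they already exist by then.
- *A reader might infer that assignments can be predicted, because block sizes are described as "permuted blocks of random size known to the researcher".* This cannot hold together with the loss of the blocks: once envelopes are mixed, there is no block sequence to predict. It matters only if the web sequence is the one used.
- *A reader might put a size on the bias.* That needs a rate of arm-related dropout and a score difference, and the documents give neither. The direction is open too: losing low scorers from control would favour control. Controls are also promised the course afterwards, which weakens the motive to leave.
- *Chance imbalance is cheap.* A 48:38 split in a stratum of 86 raises the variance of that stratum's contrast by about 1.4% ((1/48 + 1/38)/(2/43) = 1.014). It costs a little precision and creates no bias, and the total stays 86:86 if all envelopes are used.

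None of this reconciles the two procedures, restores the block order, or shows where concealment is protected.

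**Conclusion.** The point holds in this form: the protocol states incompatible allocation procedures, and the envelope version keeps neither the permuted-block order nor concealment. The conflict and the loss of block order follow directly from the text.

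Loss of stratification is conditional on both strata sharing the one large envelope. The text names a single envelope and no separation, but does not rule separation out. On that condition, an assumed stratum of 86 gives SD 6.6 for T minus C and about a 17% chance of a difference of 10 or more. Stratum and block sizes are assumptions.

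The arm may be known before consent or baseline on one plausible reading, and it is tied to an identified nurse on the other. The stronger claim, that allocation is definitely exposed before consent and baseline, is not supported. The threat is to the assumption that baseline differences are coincidental. Its size cannot be derived from the documents. The sample size of 86 per arm is not affected.

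**What to change.** 1. State one sequence in both sections: eligibility confirmed, consent signed, baseline NoMAD recorded, then one allocation at a time released by the web service already named, with unit category entered at that moment.
2. Remove the random number and the T/C code from the nomination form.
3. Delete the mixing of envelopes and their selection by participants.
4. With the web block sequence in use, say that block sizes are withheld from anyone who recruits or enrols.
5. For nurses already allocated, state which procedure was actually used, including when the code was written, whether the strata were pooled and whether baseline came before allocation, and report it with the results.

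The cost is small but not zero. Steps 1 to 4 are wording plus a service already planned, and the envelope work falls away. Step 5 needs a check of the records. Recruitment opened in July 2020, and the article says that first outcomes were available in December 2020, so rewording alone cannot change allocations already made.

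### The film of envelope preparation could become a named allocation record outside supervisor custody, and the protocol is inconsistent on when codes are linked to nurses

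*Protocol article*

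**What the plan says.** **Randomization.** Computer-generated numbers are written on the nomination forms together with the code T or C. A nurse does this, seals the forms in envelopes, mixes them and puts them into a larger sealed envelope. The text continues: "A video is made of the process of preparing the sealed envelopes, with the participant details visible". Then: "A second researcher will later view the video to ensure the accuracy of the process". On opening, it says: "Corresponding envelopes will be opened only by the participants who select them, and they will be allocated accordingly".

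**Screening for Eligibility and Enrollment.** The form that carries the code also identifies the nurse: "The data fields include name, email address, telephone number (Telegram, Viber, or WhatsApp service), current duty". Further fields include the practice unit and a box for the random number. Candidates receive the form with the invitation letter, in "numbered, opaque, sealed, and stapled envelopes that contain the nomination form for the training course", and completed forms go back to the education unit at the faculty. Later in the same section the order is consent, then a link to the baseline questionnaire, then randomization through a web-based system. The main investigator afterwards tells each participant the result.

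**Blinding.** "The randomization key (ie, document with group details) will be kept with supervisors". The supervisors release it to the researchers only after the results have been interpreted blind. A different camera recording, made when group codes are added to the data set, is assigned to supervisors.

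**The concern.** Name and arm code share one sheet of paper. Anyone who sees a completed form with its code, on paper or on film, knows that nurse's allocation. Two protections are at stake.

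The first is concealment from the person who prepares the envelopes. If names are present when T or C is written, that person could place named nurses in an arm.

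The second is the blinding of those who interpret the results. The Blinding section keeps the key from researchers, but the film goes to a researcher. Nothing says whether that person also enrolls, enters data or analyzes, whether the code is masked, or when the film is viewed.

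The Discussion concedes that participants know their arm and that the data are mainly self-reported. Concealment and blinded interpretation are therefore among the main protections left.

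**Working it through.** There is no plan figure to reproduce and no arithmetic to run. The check sets the three sections side by side and asks one question: is the participant's name on the form when the code is written and filmed?

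**Reading A: details are already on the form.**
- The filming sentence supports this, since it has participant details in view. So does the reference to corresponding envelopes.
- The preparer then sees name and code together before sealing. Opaque envelopes and later mixing do not undo this, because each form names its owner.
- Selection by participants then adds no chance element, since each envelope already belongs to someone.
- If the code is also in frame, the film pairs nurse and arm for up to 86 + 86 = 172 forms.

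**Reading B: the forms are blank at sealing.**
- The enrollment text supports this, since envelopes go out with the invitation and candidates fill in the form afterwards.
- No participant details then exist to be filmed, so the filming sentence cannot be carried out as written.
- The preparer sees numbers and codes only. The sole link between nurse and arm is the participant's choice of envelope, and the film does not show that choice.

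**A third sequence.** The later enrollment text places web-based randomization after consent and the baseline link. If coded forms are already inside the invitation envelopes, the code reaches the nurse before either step. The protocol does not say how the web-based step relates to the envelopes.

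**Custody.**

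| Item | Who sees or holds it | Section |
|---|---|---|
| Randomization key | Supervisors, until blinded interpretation is final | Blinding |
| Recording of codes being added to the data set | Supervisors | Blinding |
| Film of envelope preparation | A second researcher, at an unspecified later time | Randomization |

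The Blinding section treats supervisors and researchers as different groups. On its wording, the film's viewer belongs to the group from which the key is withheld, unless this researcher is in fact a supervisor.

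**What the text leaves open.** It does not say that T or C can be read on the film. A check of accuracy makes that likely, because the code is written on the filmed form, but it remains an inference. Nor does it say that the film is viewed before envelopes are opened.

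**The case against.** The strongest reply is that the film is an audit step that deters tampering, and that no breach is documented. Only participant details are said to be visible, not the code. The second researcher could be a supervisor. Someone always handles the codes when envelopes are prepared, with or without a camera. With blank forms, mixing and free selection, neither preparer nor viewer would know who receives which arm. Viewing after sealing cannot change what was sealed. In addition, the main investigator learns every allocation anyway, by telling participants their result and then tracking module completion in the intervention group (Process of Implementation). Finally, a condensed article may leave role details to a fuller document.

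Much of this stands. It rules out the stronger inference that a reader might draw, namely that a second copy of the key exists in a researcher's hands and that allocation was open at sealing. Both need facts that the protocol does not state.

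It does not remove the point. The blank-form defense works only if the filming sentence is wrong, and the filming sentence works only if names are present. This is a contradiction in what is written, not a detail left out. The main investigator's knowledge of allocations is a separate conflict with the Blinding section. It reduces what the film adds to unblinding but does not protect concealment from the preparer.

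**Conclusion.** The point holds in a limited form. The protocol contradicts itself on when codes are linked to participants, and it adds a possible route to disclosure without stating a safeguard. On Reading A, the preparer can link names to arms before sealing, and the film may hold identifiable allocations outside supervisor custody. On Reading B, the filming instruction cannot be followed.

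The extent is up to 172 forms if details are on all of them at preparation, and none if the forms are blank. No shift in the NoMAD comparison can be derived. That would need the number of nurses steered and how they differ, and the protocol supports no value for either. Any such figure would be assumption alone.

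The conclusion rests on the wording of the three sections and on the form carrying both name and code. It does not assume that anyone misused the information. This is a modest procedural weakness, worth correcting because correction is nearly free.

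**What to change.** 1. Reconcile the Screening for Eligibility and Enrollment and the Randomization sections into one sequence. State when the code is written, when the participant's details are added, how the web-based step relates to the envelopes, and whether participants choose an envelope or receive one assigned to them. The sequence has to agree with the stated order of consent, baseline questionnaire and then randomization.
2. Write, seal and film the codes with only the random number and code in view, before any participant detail is on the form.
3. Have the film checked by the supervisors who already hold the key. Otherwise, state that the viewer has no role in enrollment, data entry, analysis or interpretation.
4. The article reports that recruitment opened in July 2020. For envelopes already prepared, report what the film showed, who viewed it and when.

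The cost is a few sentences and a change of camera framing. Supervisors already handle the other recording, so no extra staff are needed, and sample size and analysis are unchanged. The accuracy check is kept. These changes do not resolve the separate conflict between the main investigator telling participants their allocation and the blinded investigators described under Blinding. That needs its own correction.
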